### Statistical Analysis

#### Power

Factorial trials can be powered to detect either main effects or interaction effects, depending on the anticipated influence of interactions within the trial context [92]. This trial was powered to detect the main effects of the PrEP4T and LS4TM interventions. The trial was not powered to detect a PrEP4T × LS4TM interaction effect because (1) based on our conceptualization, the interventions were distinct in delivery (individualized vs group based) and content (peer navigation vs. community support and IMB strategies), and informed by preliminary studies and knowledge of the study population, we did not anticipate a combined interaction effect; and (2) any potential interaction was expected to be negligible, described in factorial trials as a minor “small quantitative interaction” [92-94]. Both PrEP4T and LS4TM were distinct, peer-delivered digital interventions that TMSM endorsed for HIV prevention in our prior research. We hypothesized that each strategy would independently increase PrEP uptake by at least 20% among TMSM, addressing the main-effects research question. Although we did not anticipate interaction effects, we hypothesized additive effects such that participants assigned to the PrEP4T + LS4TM condition would achieve the highest PrEP uptake rates. These superiority hypotheses were supported by evidence from a systematic review of peer-delivered interventions [47].

We estimated PrEP uptake rates in the SOC condition based on prior TMSM data [8,15] and conducted simulations using an SAS macro [95]. Simulations varied the number of participants per condition (n=40-120) and the magnitude of intervention effects over 18 months (20%-40%) for the PrEP4T and LS4TM conditions. Assuming 10% attrition, a total sample size of 300 (75 per condition) provided 80% power or greater to detect a 20% increase in PrEP uptake for each intervention versus SOC at a .05 significance level. We selected a 20% increase because smaller differences were not considered clinically meaningful for potential scale-up. To account for attrition, we planned to enroll 375 participants at baseline, anticipating approximately 20% loss to follow-up, resulting in 300 participants completing the study.

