Aim 2 will use causal inference methods from epidemiology [96,97] to conduct mediation analyses and examine the mechanisms of action for the interventions. Mediation analyses will estimate the natural direct and indirect effects of proposed mediators—health care empowerment, TMSM community connectedness, and IMB constructs—on the relationship between intervention condition and PrEP uptake compared with SOC. Mediation models will be implemented using a series of random-effects logistic regression models, consistent with the approach described in aim 1.

For aims 1 and 2, patterns of missingness will be examined, and baseline responses will be compared between participants with and without missing data. Variables associated with missingness will be included in the analyses to yield valid inferences [98]. Modern missing data techniques [99] will be employed, with multiple imputation used to handle missing data, including participants lost to follow-up [100]. Sensitivity analyses will compare parameter estimates from completer-only analyses with those from multiple imputation to assess potential bias.

Aim 3 qualitative data from IDIs will be analyzed to explore PrEP decision-making and participant experiences with the interventions. An iterative analytic process will follow Crabtree and Miller’s [101] 5-step approach: (1) describing, (2) organizing, (3) connecting, (4) corroborating, and (5) representing. Regular debriefing meetings with data collectors will identify preliminary findings and guide iterative data collection and analysis. An initial set of codes will be developed based on the study’s conceptual frameworks of Healthcare Access, Gender Affirmation, and IMB constructs. Qualitative codes will be applied to transcripts and interview notes using qualitative analysis software by 2 independent analysts. New codes will be added as themes emerge. Summaries will be created for major themes and differences across subgroups. Descriptive quantitative survey data (eg, demographics, social and medical gender affirmation) may be used to contextualize qualitative findings. CAB members will provide ongoing input and help corroborate the qualitative results.

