#### Refinement of Study Design

The initial study design included a 3-month run-in period intended to reduce study attrition and mitigate loss-to-follow-up among participants who might enroll solely to complete the baseline assessment and HIV testing for the incentive. However, the CAB recommended removing the run-in period, noting that the waiting period could discourage participation, create unnecessary anxiety while participants awaited the interventions, and erode trust with the community, given the historical mistrust in medical and research settings due to discrimination and mistreatment.

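### Comparing completers with multiple imputation cannot assess bias from dropout related to unobserved PrEP uptake, so its stated purpose is too broad

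*Protocol article*

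**What the plan says.** Under Data Analysis by Aim, the Protocol article sets one missing-data strategy for aims 1 and 2. Missingness patterns are examined and "baseline responses will be compared between participants with and without missing data". Then "Variables associated with missingness will be included in the analyses to yield valid inferences", and modern techniques are applied, "with multiple imputation used to handle missing data, including participants lost to follow-up". One sensitivity analysis is named: "Sensitivity analyses will compare parameter estimates from completer-only analyses with those from multiple imputation to assess potential bias".

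Four other sections bear on how much weight that check must carry:

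- **Power:** 375 are to be enrolled, "anticipating approximately 20% loss to follow-up, resulting in 300 participants completing the study". The same section also says: "Assuming 10% attrition, a total sample size of 300 (75 per condition) provided 80% power or greater".
- **Randomization and Blinding:** participants and intervention staff are not blinded.
- **Incentives and Disbursement:** each attended session is paid, with six sessions per intervention. Condition A therefore has 0 paid sessions, B and C have 6, and D has 12.
- **Refinement of Study Design:** the initial design had a 3-month run-in, partly because of "participants who might enroll solely to complete the baseline assessment and HIV testing for the incentive". The community advisory board recommended removing it, and Study Procedures describes none.

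**The concern.** Completer-only analysis and standard multiple imputation both use observed data to stand in for what was not observed. If, given arm and observed covariates, people who leave differ in PrEP uptake from people who stay, both estimates are off, and they can be off by much the same amount. Close agreement between them would then be read as reassurance that it does not provide.

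The check is weakest for people who leave soon after baseline. They have no follow-up outcomes, so the imputation has only their arm and baseline answers to work with. That is the group the run-in was meant to reduce. Retention could also differ by arm, since participants know their assignment and the arms differ in paid contact. The Power section treats increases below 20% as not clinically meaningful, so a bias of a few points could change the conclusion.

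**Working it through.** **1. The plan's own figure.** 300 / (1 − 0.20) = 375, which matches the planned enrollment. Up to 375 − 300 = 75 people would be lost by the end of the study, or about 375 / 4 ≈ 94 randomized and 19 lost per arm.

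**2. Assumptions.** The article gives no SOC uptake rate and does not say whether the 20% increase is absolute or relative. I assume uptake among those retained of 0.20 in SOC and 0.40 in an intervention arm. I also assume that observed covariates say nothing further about the missing outcomes, so that completers and imputation both centre on 0.20. The loss rates by arm and the uptake among the lost are assumptions too.

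**3. Difference among all randomized.** Let m₀ and m₁ be the fractions lost (SOC, intervention), and u₀ and u₁ the uptake among the lost:

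D = [(1 − m₁)·0.40 + m₁·u₁] − [(1 − m₀)·0.20 + m₀·u₀]

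| m₀ | m₁ | Uptake among the lost | D |
|---|---|---|---|
| 0.20 | 0.20 | equal in both arms (u cancels) | 0.32 − 0.16 = 0.16 |
| 0.10 | 0.20 | none | 0.32 − 0.18 = 0.14 |
| 0.20 | 0.10 | none | 0.36 − 0.16 = 0.20 |
| 0.20 | 0.20 | odds half those of the retained: 0.111 SOC, 0.25 intervention | 0.370 − 0.182 = 0.188 |
| 0.10 | 0.10 | equal in both arms | 0.36 − 0.18 = 0.18 |

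Extreme bounds, with all of the lost in one arm taking up PrEP and none in the other:

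- 20% lost per arm: 0.8 × 0.20 ± 0.20, or −0.04 to 0.36.
- 10% lost per arm, the other attrition figure in the Power section: 0.9 × 0.20 ± 0.10, or 0.08 to 0.28.

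**4. Does the planned comparison react?** This was simulated 1,500 times with 94 per arm, a true difference of 0.20, 20% loss per arm, and a prognostic baseline covariate in the imputation model. In the informative case, intervention-arm loss is 30% without uptake and 5% with uptake (0.6 × 0.30 + 0.4 × 0.05 = 0.20 overall). SOC loss is unrelated to uptake.

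| Dropout | Full data | Completers | Multiple imputation | Mean absolute gap, completers vs imputation |
|---|---|---|---|---|
| Informative | 0.199 | 0.273 | 0.269 | 0.009 |
| Non-informative | 0.200 | 0.200 | 0.199 | 0.008 |

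A hand check of the informative case: retained uptake in the intervention arm is 0.4 × 0.95 / 0.80 = 0.475, and 0.475 − 0.20 = 0.275, close to the simulated 0.273. Both planned estimates are too high by about 0.07, yet they differ from each other no more than they do when dropout is harmless.

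**The case against.** The other side has a substantial case.

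- **The comparison is not useless.** If observed variables predict both dropout and uptake, imputation can move away from the completer estimate, and that movement reveals bias. Assessments and Survey Measures lists baseline PrEP cascade, motivation, self-efficacy and barrier items. Later dropouts also leave interim surveys. A reader might infer that the comparison can assess no bias at all, or that imputation simply gives leavers the uptake of engaged participants. The planned use of these variables does not support either reading.
- **The article does not predict outcome-dependent dropout.** A reader might infer from Refinement of Study Design that leavers are the people least likely to start PrEP. That section describes incentive-driven enrollment and links it to neither PrEP uptake nor arm. The mechanism is plausible, not documented.
- **Other analyses may exist.** A reader might take this to be the trial's only missing-data sensitivity analysis. That holds for the article alone. The full protocol and SAP are not shown, and the absence of a tipping-point analysis here is not in itself a fault.
- **The figures depend on the inputs.** Reversing the unequal loss removes the bias on the risk-difference scale, and extra paid contact could as easily favor retention in the intervention arms. The planned model is logistic. With 20% lost per arm and no uptake among the lost, the simple odds ratio moves only from (0.40/0.60)/(0.20/0.80) = 2.67 to (0.32/0.68)/(0.16/0.84) = 2.47.
- **The 20% is loss by study end.** People who leave later still contribute earlier outcomes to the repeated-measures model, and the Power section also uses 10%.

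All of this stands and limits the point. It does not remove it: the article gives this comparison a general purpose, and the comparison serves only part of it.

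**Conclusion.** The point holds in limited form. The stated comparison can show bias explained by observed predictors of missingness. It cannot assess bias from dropout related to unobserved PrEP uptake, and agreement between the two estimates is no evidence against such bias.

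The size cannot be fixed from the article. Under the assumed 20% and 40% uptake among those retained, the illustrated differences run from 14 to 20 points where the planned analyses centre on 20. The simulated case instead has both analyses overstating a true 20 points by about 7. At 20% loss per arm the extreme bounds, −4 to 36 points, span 40 points, twice the 20-point effect if that target is read as absolute. None of these figures predicts what would happen in this trial.

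The award was terminated with 103 enrolled, but the article still states the analyses prospectively, and a smaller sample makes an untested missing-data assumption no safer.

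**What to change.** 1. Keep multiple imputation as the primary analysis, and keep the completer comparison as a descriptive result.
2. Limit the stated purpose of that comparison to bias explained by observed variables.
3. Add delta-adjusted multiple imputation by arm. Shift the log-odds of uptake among the missing over a grid stated in advance, let the shift differ between arms, and report the shift at which the conclusion changes (the tipping point).
4. Include missing = no uptake as one labelled scenario. It is a single extreme assumption and should not serve as the reference analysis.
5. Reconcile the 10% and the approximately 20% attrition in the Power section, so that the expected missing fraction is clear when the grid is chosen.

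If the full protocol or SAP already contains item 3, only the wording change in item 2 and the reconciliation in item 5 remain. The cost is a few extra imputation runs and additional sensitivity results to report and explain. No data collection changes.

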#### Data Analysis for Protocol Manuscript

Descriptive statistics were calculated for cumulative enrollment numbers, recruitment activities, screener and baseline survey completions, and sociodemographic characteristics of enrolled participants. To evaluate the effectiveness of different recruitment strategies, Granger causality tests [102] were conducted to forecast screening and baseline survey completions based on recruitment activity types; *F* tests on lagged values were used to determine whether recruitment strategies statistically predicted future screening and enrollment completions at 1- and 2-week intervals following recruitment activities, with significance set at an α level of .05. Trends over time were visualized graphically.

### Ethical Considerations

The Fenway Institute at Fenway Health served as the single institutional review board of record (institutional review board protocol approval number 2023-12). Written informed consent was obtained from all participants before initiating any study procedures. Extensive safeguards were implemented to protect participant information and ensure privacy and confidentiality, including storing participant names and contact information separately in password-protected files from deidentified survey data and HIV testing results. The study was protected by a Certificate of Confidentiality from the NIH. Participants were compensated for their involvement (see the “Incentives and Disbursement” section). A Data Safety and Monitoring Board was established to oversee the trial’s progress, review safety data, and provide recommendations on whether the trial should continue based on its assessment of safety and research performance. The board convened at least annually.

## Results

### Community Advisory Board Collaboration in Study Start-Up Activities

#### Overview

Monthly or bimonthly meetings of the virtual CAB ensured close collaboration and active participation with the research team. All study protocols and procedures were codeveloped and refined with CAB input to maximize acceptability for the study population. The CAB provided invaluable guidance throughout the study.

#### Study Population Definitions

Discussions with the CAB focused on defining and operationalizing the study population of “TMSM” to maximize inclusivity while targeting those at risk for HIV. This included considerations of gender identity (transgender men, nonbinary people, transmasculine individuals, and other gender-diverse people), sexual orientation identity (gay, bisexual, queer, and other diverse identities), and behavioral HIV risk criteria (gender and anatomy of sexual partners).

#### Operationalization of Geographic Stratification

Geographic stratification for randomization was discussed, focusing on ensuring balance across EHE geographic hot spots and capturing the geo-sociopolitical climate, including policy contexts that could influence PrEP access and the lived experiences of TMSM. The decision to incorporate MAP legislative maps resulted from consultation with the CAB.

#### Refinement of Study Design

The initial study design included a 3-month run-in period intended to reduce study attrition and mitigate loss-to-follow-up among participants who might enroll solely to complete the baseline assessment and HIV testing for the incentive. However, the CAB recommended removing the run-in period, noting that the waiting period could discourage participation, create unnecessary anxiety while participants awaited the interventions, and erode trust with the community, given the historical mistrust in medical and research settings due to discrimination and mistreatment.

#### Branding and Detailed Recruitment Plan

A study logo, branding, website, and recruitment materials were developed to promote diverse participation across race, ethnicity, and geographic regions (see Tables S3 and S4 in Multimedia Appendix 1). Digital flyers and online advertisements were created in collaboration with a paid consultant who was a member of the community. A detailed, stepwise recruitment plan with targeted dates was established to implement different strategies, enabling the team to track screening and enrollment numbers and evaluate the effectiveness of each recruitment approach.

### Recruitment and Enrollment

Recruitment and enrollment began on February 1, 2024. Cumulative recruitment and enrollment numbers from February 2024 to March 2025 are shown in Figure 3. Recruitment activity types are represented by colored dashed lines, while completed screeners and completed baseline surveys are shown as solid orange and blue lines, respectively.

**Figure 3 figure3:**
[figure not shown]
Cumulative recruitment and enrollment numbers by recruitment activity type (dashed lines), completed screeners (orange line), and completed baseline surveys (blue line), February 2024-March 2025.

Granger causality tests were conducted to forecast screening and baseline enrollment survey completions based on recruitment activity types (Table 4). The most effective strategies for 2-week baseline survey completions were closed Facebook groups (*F*_2,23_=6.52, *P*=.006) and Lex (*F*_2,23_=4.63, *P*=.02). Lex also significantly predicted screening completions at both 1 week (*F*_1,26_=10.41, *P*=.003) and 2 weeks (*F*_2,23_=6.18, *P*=.007).

**Table 4 table4:** Granger causality test forecasting the effect of recruitment efforts^a^ on screener and baseline enrollment survey completion with 1- and 2-week lag times, February 2024-March 2025.

Recruitment category	Survey type	Granger *F* test (*df*)^b^ for 1-week lag	*P* value^b^	Granger *F* test (*df*) for 2-week lag	*P* value^b^
Dating app	Screened	0.40 (1, 26)	.53	0.28 (2, 23)	.76
Dating app	Baseline survey	1.70 (1, 26)	.20	1.06 (2, 23)	.36
Facebook	Screened	0.58 (1, 26)	.45	0.43 (2, 23)	.65
Facebook	Baseline survey	0.07 (1, 26)	.80	6.52 (2, 23)	*.006*
Health care/nonprofit organization	Screened	1.44 (1, 26)	.24	1.16 (2, 23)	.33
Health care/nonprofit organization	Baseline survey	2.64 (1, 26)	.12	2.05 (2, 23)	.15
Lex	Screened	10.41 (1, 26)	*.003*	6.18 (2, 23)	*.007*
Lex	Baseline survey	1.17 (1, 26)	.29	4.63 (2, 23)	*.02*
Reddit	Screened	0.43 (1, 26)	.52	0.21 (2, 23)	.81
Reddit	Baseline survey	0.48 (1, 26)	.49	2.69 (2, 23)	.09

^a^Recruitment effort represents the contacting of an organization or posting of social media or dating app advertisements.

^b^Italicized *P* values indicate statistical significance at =.05.

As of March 20, 2025, 103 TMSM were enrolled (Table 5). The median age was 26 (IQR 24-31) years. Among the 103 participants, 39 (37.9%) identified as BIPOC and 18 (17.5%) identified as Latine. The most frequently reported gender identities were “transgender men or trans man” (36/103, 35%); transmasculine (31/103, 30.1%); and nonbinary, genderqueer, or gender nonconforming (15/103, 14.6%). The majority of participants had socially, legally, and medically affirmed their gender identity. Participants reported diverse sexual orientation identities, with 67 (65%) identifying as queer, 38 (36.9%) as bisexual, 37 (35.9%) as gay, and 18 (17.5%) as pansexual (totals exceed 100% due to a “select all that apply” response format). The sample was highly educated: 69 (67%) had a 4-year college degree or higher, and 24 (23.3%) were full-time students. A small proportion (7/103, 6.8%) reported having no health insurance.

**Table 5 table5:** Sociodemographics of enrolled participants (N=103).

Sociodemographics		Values
Age in years, median (IQR)		26 (24-31)
**Categorical age (years), n (%)**		
	18-24	36 (35.0)
	25-29	33 (32.0)
	30-39	28 (27.2)
	40+	5 (4.9)
	Missing	1 (1.0)
**Gender identity (single option), n (%)**		
	Man	13 (12.6)
	Male	1 (1.0)
	Man of transgender experience	2 (1.9)
	“Transgender man or trans man”	36 (35.0)
	Female-to-male	3 (2.9)
	Transmasculine	31 (30.1)
	Nonbinary	7 (6.8)
	Genderqueer	6 (5.8)
	Gender nonconforming	2 (1.9)
	Agender	2 (1.9)
**Sexual orientation (select all-that-apply), n (%)**		
	Straight or heterosexual	1 (1.0)
	Gay	37 (35.9)
	Bisexual	38 (36.9)
	Queer	67 (65.0)
	Pansexual	18 (17.5)
	Asexual	2 (1.9)
	Demisexual	10 (9.7)
	Questioning or unsure	2 (1.9)
	I do not label my sexual orientation	9 (8.7)
	Another sexual orientation	5 (4.9)
**Racial identity, n (%)**		
	White	64 (62.1)
	Asian	5 (4.9)
	Black or African American	5 (4.9)
	Latino/e or Hispanic	8 (7.8)
	Multiracial	21 (20.4)
**Latino/ethnicity, n (%)**		
	Yes	18 (17.5)
	No	85 (82.5)
**Health insurance type^a^, n (%)**		
	No health insurance	7 (6.8)
	Public health insurance	17 (16.5)
	Private health insurance	79 (76.7)
**US Census region, n (%)**		
	Midwest	21 (20.4)
	Northeast	30 (29.1)
	South	30 (29.1)
	West	19 (18.4)
	Ending the HIV Epidemic Area, not specified	3 (2.9)
**Highest educational attainment, n (%)**		
	High school diploma or General Educational Development	6 (5.8)
	Associate’s degree/trade school certification	3 (2.9)
	Some college or university	25 (24.3)
	Bachelor’s degree	43 (41.7)
	Some graduate school	10 (9.7)
	Graduate degree	16 (15.5)
**Current student status, n (%)**		
	No	72 (69.9)
	Yes, part time	7 (6.8)
	Yes, full time	24 (23.3)
**Outwardly express gender identity full time, n (%)**		
	Yes	91 (88.3)
	No	12 (11.7)
**Any legal gender affirmation^b^, n (%)**		
	Yes	79 (76.7)
	No	24 (23.3)
**Gender-affirming hormone use (testosterone), n (%)**		
	Yes, within the last 3 months	94 (91.3)
	Yes, but not in the last 3 months	8 (7.8)
	Missing	1 (1.0)
**Any history of gender-affirming surgery, n (%)**		
	Yes	75 (72.8)
	No	28 (27.2)

^a^Participants could report more than 1 type of health insurance. If a participant reported both public and private insurance, they were coded as having private insurance. Additionally, participants who reported coverage through an employer, parents, partner, or college/university were also coded as having private insurance.

^b^Any legal gender affirmation was operationalized as having at least one identification document that listed the participant’s affirmed name or gender.

